#### Statistical analysis

The primary analysis will be based on the intention-to-treat principle.

##### Primary study parameter(s)

The primary endpoint (proportion of *S. aureus* eradication during a 1-year time period, using logistic mixed models) will be expressed in terms of odds ratios and 95% confidence intervals (CI). If the 95% CI does not contain value 1, we can conclude that either of the strategies is significantly different from the other.

We choose a logistic mixed-effect model because it is a linear model that fits best for this longitudinal study using repeated dichotomous measures. In addition, logistic mixed-effects models have a better distinguishing ability. It is expected that this results in an even greater power than the more simplistic area under the curve model that was used for the power analysis.

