### Outcome measures

*Primary outcome*
Proportion of patients in whom *S. aureus* is totally eradicated during a 1-year time period.Total eradication is defined as 100% of all swabs (nose, throat, rectum, exit-site catheter, and body regions on indication) being negative for *S. aureus* per measured time point.
*Secondary outcomes*
Secondary outcomes are listed in Table 1.

**Table 1 Tab1:** Secondary outcome measures

Secondary outcome measure	Data collection instrument or method
Incidence of *S. aureus* infections	(S)AE forms every 3 months
Overall incidence of infections	(S)AE forms every 3 months
Mortality	Data from electronic patient file
Long-term antimicrobial resistance	Culture results every 6 months and NGS
Number of catheter removals	Data from electronic patient file
Time to first catheter-related infection	(S)AE forms every 3 months and data from electronic patient file
Successful *S. aureus* eradication per body site	Culture results
Relapse rate of *S. aureus* carriage	Culture results and NGS
Transmission routes	Caregivers culture results and NGS
*S. aureus* transmission routes	NGS
Adverse events	(S)AE forms every 3 months
Predictors for infections and treatment failure or success	Binominal regression analysis
Patient compliance	Medication files, counting pills, trial-specific medication diary, modified Morisky Medication adherence questionnaire
Generic health related quality of life	EuroQol 5 dimension, 5 levels questionnaire (EQ5D-5 L)
Treatment satisfaction	TSQM vII questionnaire
Healthcare related costs	iMCQ questionnaire

*iMCQ* iMTA Medical Consumption Questionnaire, *NGS* next-generation sequencing, *(S)AE* (serious) adverse event, *TSQM* Treatment Satisfaction Questionnaire for Medication

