### Analysis

#### Sample size and power calculation

Hardly any literature is available regarding long-term efficacy of the CS group on total *S. aureus* carriage eradication. Even when articles describe similar eradication strategies as the CS group, endpoints vary from only local, nasal *S. aureus* eradication to *S. aureus* infections. Consequently, total body site (de)colonization has not been described thoroughly. Based on a few studies with quite similar eradication strategies, it is, however, possible to make an assumption about the long-term efficacy [10, 13–16]. The eradication rate of the SD strategy group is expected to be 77% and for the CS strategy group 55% over 1 year. Based on the settings binary outcome (carriage yes/no), superiority trial, power (1 − β) of 80% and a significance level (α) of 5%, a total of 138 patients (2 × 69) are required to detect a significant increase from 55 to 77%.

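### The stated endpoint, the sample size and the primary model describe different quantities: a proportion of patients over 1 year is tested with a conditional odds ratio from repeated visit results

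*Protocol article*

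**What the plan says.** Under Outcome measures, the primary outcome is "Proportion of patients in whom *S. aureus* is totally eradicated during a 1-year time period". The definition that follows calls a patient totally eradicated when all swabs are negative, but applies this time point by time point: "being negative for *S. aureus* per measured time point". No rule turns several time points into one result per patient.

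Under Sample size and power calculation, the planning assumption is: "The eradication rate of the SD strategy group is expected to be 77% and for the CS strategy group 55% over 1 year". The calculation is described as "Based on the settings binary outcome (carriage yes/no), superiority trial", with 80% power and 5% significance, giving 2 × 69 patients.

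Under Primary study parameter(s), the endpoint is given as "proportion of *S. aureus* eradication during a 1-year time period, using logistic mixed models". The model is chosen because it "fits best for this longitudinal study using repeated dichotomous measures". The decision rule is: "If the 95% CI does not contain value 1, we can conclude that either of the strategies is significantly different from the other". The section also expects "even greater power than the more simplistic area under the curve model that was used for the power analysis".

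Under Follow-up, all patients give swabs at months 3, 6, 9 and 12.

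**The concern.** The endpoint and the sample size take the patient as the unit. The primary model takes the visit as the unit and reports an odds ratio that holds for a given value of the patient's random effect. No time point or treatment-by-time contrast is attached to the decision rule, so the natural reading is one treatment effect pooled over visits. The power analysis is also described in two ways: as a binary comparison in one section, and as an area-under-the-curve model in another.

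Two things are at stake. First, a reader would take the reported odds ratio as the effect on the proportion of patients eradicated, which it does not estimate. Second, the arms may plausibly differ in time course. Under Study intervention, search and destroy is a short course with retreatment on relapse, whereas continuous suppression repeats monthly. With different time courses, a pooled visit-level test and a patient-level test can part company.

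**Working it through.** SD means search and destroy, CS means continuous suppression, and σ is the standard deviation of the random intercept.

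**1. The plan's own sample size.** The inputs are 77%, 55%, 80% power and 5% significance from Sample size and power calculation. Significance is taken as two-sided, as stated under Secondary study parameter(s). Unpooled two-proportion formula:

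n = (1.96 + 0.8416)² × (0.55 × 0.45 + 0.77 × 0.23) / 0.22² = 7.849 × 0.4246 / 0.0484 = 68.86, so 69 per arm and 138 in total.

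The stated figure is reproduced. Power at 69 per arm is 80.1% (unpooled) or 78.5% (pooled variance). No number of visits, within-patient correlation or area under a curve enters. The 138 is the size for one binary result per patient.

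**2. Scale of the odds ratio.** Marginal OR = (0.77/0.23) / (0.55/0.45) = 2.74.

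For the mixed model, logit P(negative | b) = η + b with b ~ N(0, σ²). In each arm η is solved so that the average over b equals 0.77 or 0.55. The conditional OR is exp(η_SD − η_CS). If 77% and 55% are per-visit rates, the share negative at all four visits is the average of P(negative | b)⁴. The documents give no σ, so 1 to 3 is an assumed range.

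| σ | Conditional OR | Negative at all four visits, SD vs CS |
|---|---|---|
| 1 | 3.32 | 43% vs 17% |
| 2 | 5.07 | 53% vs 27% |
| 3 | 8.45 | 59% vs 34% |

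**3. Month-12 status equal.** Simulation with 69 per arm and four visits. The model has arm and visit effects, a random intercept and no treatment-by-visit term, with a likelihood-ratio test at 5%. There were 200 runs per cell, so the Monte Carlo standard error is at most √(0.5 × 0.5/200) = 3.5 points. Trajectories are assumed. Entries are for σ = 1 / 2 / 3; the first row is a constant-effect reference.

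| Negative at months 3, 6, 9, 12 | Mixed model favours SD | Month-12 test rejects | All-visits test rejects |
|---|---|---|---|
| SD 77% vs CS 55% throughout | 100 / 96.5 / 94.5% | 85.5 / 79.5 / 82% | 91.5 / 89 / 86% |
| SD 85, 80, 70, 60 vs CS 40, 50, 55, 60 | 99.5 / 95 / 92.5% | 2 / 4.5 / 6.5% | 89 / 83.5 / 74.5% |
| SD 77, 77, 77, 55 vs CS 55 throughout | 92.5 / 81.5 / 68.5% | 2.5 / 3 / 7% | 61.5 / 47 / 39% |
| SD 77, 70, 62, 55 vs CS 55 throughout | 54 / 46 / 38% | 5 / 5 / 6% | 28.5 / 26.5 / 17% |

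**4. All-visits-negative status equal.** Here the share of patients negative at all four visits is the same in both arms, but the per-visit rate and the within-patient correlation differ.

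| SD per-visit rate (σ) | CS per-visit rate (σ) | All visits negative, both arms | Mixed model favours SD | All-visits test rejects |
|---|---|---|---|---|
| 77% (0) | 56.4% (3) | 35.2% | 91.5% | 6% |
| 77% (0.5) | 58.8% (3) | 37.7% | 83% | 6.5% |
| 77% (1) | 63.7% (3) | 43.0% | 57% | 4% |
| 70% (1) | 60.7% (2) | 32.8% | 32.5% | 5.5% |

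On either patient-level reading, the pooled visit-level test can reject when the patient-level proportion is the same in both arms.

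**The case against.** The strongest reply is that the article means a whole-year, repeated-status endpoint. Its time-point definition, its choice of model and its mention of an area under the curve all point that way, and a mixed model suits such an endpoint. This largely stands as a reading. It does not remove the conflict, because the endpoint is still worded as a proportion of patients and the sample size reproduces as a single binary comparison.

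Four stronger readings are tempting, and the documents do not support them:

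- A reader might infer that the trial would wrongly declare long-term superiority whenever month-12 rates are equal. Month 12 is never named as the target. In the step 3 trajectories with equal month-12 rates, the arms truly differ over the year. For example, 77, 77, 77, 55 averages 71.5% against 55%, and the all-visits share at σ = 1 is 33% vs 17%. Those rejections are errors only if month 12 is the target.
- A reader might infer that the conditional odds ratio makes the test invalid. With a constant effect and a common σ, the conditional and marginal odds ratios both equal 1 under the null. The scale gap then concerns interpretation and does not change the decision.
- A reader might infer that the weekly post-treatment swab sets, taken only in SD, enter the model. Study intervention sets these apart from the 3-monthly rounds, and Follow-up gives all patients the same four visits.
- A reader might infer that 138 is wrong, or that analysts following the text must reach opposite conclusions. The number is reproduced, and the article names one model and one decision rule.

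The pooled form is also an inference. The article lists no fixed effects, and a full analysis plan may add a treatment-by-visit term. The single-interval rule and the power gain expected from repeated measures fit a pooled effect but do not prove one.

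**Conclusion.** The point holds as an inconsistency in what the article itself fixes: the endpoint, the effect measure, the decision rule and the planning calculation do not describe one quantity. An unseen analysis plan could settle this only by departing from one of those statements.

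Its size has two parts. For the planning rates, the model's odds ratio would exceed the marginal one by a factor of about 1.2 to 3.1 (3.32/2.74 to 8.45/2.74). In the assumed scenarios, the pooled test favours SD in 38% to 99.5% of runs when month-12 status is equal, and in 32.5% to 91.5% when all-visits status is equal. These ranges rest on assumed trajectories, assumed σ and a model without a treatment-by-visit term. They show that the choice of quantity can decide the result, not how likely that is in this trial. This should be fixed, but it does not show that the planned test is invalid.

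**What to change.** State one primary quantity and make the analysis match it. Either route works:

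- **(a) Patient-level.** Define a rule over the scheduled month 3, 6, 9 and 12 sets, including how missed sets count. Analyse it with a logistic model adjusted for country (the stratification factor), and report the standardised risk difference and marginal odds ratio with 95% confidence intervals.
- **(b) Visit-level.** Keep the mixed model as primary on the four common visits. Restate the endpoint as the probability of being eradicated across scheduled visits in the year. Include visit and treatment-by-visit terms, name the contrast that carries the decision, and report standardised marginal proportions per visit and over the year.

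In either case, reconcile the area-under-the-curve remark with the binary sample-size calculation, and say whether 77% and 55% are patient-level or per-visit rates.

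Cost: no new data, and wording changes that can be made before database lock. Route (a) may lose some power if the effect is constant over time, as the constant-effect row in step 3 shows. An all-visits rule would also count a relapse that is later cleared as a failure. Route (b) needs only wording and some extra reporting.

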##### Secondary study parameter(s)

Continuous data such as patient characteristics (age, sex, venous access, CRBSIs) will be presented as means ± standard deviation and in case of skewed distributions as medians and range. Dichotomous outcomes will be summarized as percentages (N events/N total). Parameters will be compared between both groups by the Student’s *t*-test, Wilcoxon rank sum test, Chi2-test or Fischer exact test depending on the type of outcome and distribution. A two-tailed *p* value < 0.05 is considered statistically significant. No corrections for multiple tests are applied. Known predictors (such as socio-economic status, pet ownership, location of *S. aureus* carriage, *S. aureus* carriage by caregiver, and active skin disease) for infections and treatment failure/success will be analyzed using a logistic and/or linear regression model.

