**Methods/design:**

The CARRIER trial is a randomized, open-label, multicenter clinical trial in Dutch and Danish hospitals that treat patients on HPN. A total of 138 adult HPN patients carrying *S. aureus* will be randomly assigned to a search and destroy (SD) strategy, a quick and short, systemic antibiotic treatment, or a continuous suppression (CS) strategy, a repeated chronic topical antibiotic treatment. The primary outcome measure is the proportion of patients in whom *S. aureus* is totally eradicated during a 1-year period. Secondary outcomes are time to successful eradication, long-term antimicrobial resistance, adverse events, patient compliance, incidence of (*S. aureus*) infections, catheter removals, mortality rates, *S. aureus* transmission routes, quality of life, and health care costs.

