#### Follow-up

Patients will be followed for 1 year. At months 6 and 12, swabs will be obtained at the outpatient clinic and questionnaires regarding adverse events (AEs) will be collected. In between outpatient visits, at 3 and 9 months, swabs will be sent to the laboratory and patients will be interviewed via telephone to assess adverse events and treatment satisfaction with a validated questionnaire (TSQM vII). At inclusion and 6 and 12 months, generic health-related quality of life and health care costs will be measured with questionnaires as well (EQ-5D-5 L, iMCQ). Discontinuation of study treatment by patients will be recorded, including the reason for discontinuation. If possible, a final visit procedure (collecting swabs 1 year after inclusion) will be performed.

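### The four tests named for all secondary comparisons cannot handle censored infection times or unequal exposure; false differences arise only if follow-up differs between arms

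*Protocol article*

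**What the plan says.** Under Secondary study parameter(s), the article describes how continuous data are summarised and says "Dichotomous outcomes will be summarized as percentages (N events/N total"). It then states that parameters will be compared between the groups by the Student t-test, "Wilcoxon rank sum test, Chi2-test or Fischer exact test depending on the type of outcome and distribution", two-tailed at 0.05. The only other secondary method is for predictors: "treatment failure/success will be analyzed using a logistic and/or linear regression model". The logistic mixed model is reserved for the primary endpoint. No survival or rate method appears anywhere in the article.

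Table 1 (Outcome measures) lists "Time to first catheter-related infection", "Overall incidence of infections" (and, separately, *S. aureus* infections) and "Number of catheter removals". The Abstract adds an outcome that Table 1 does not list: "Secondary outcomes are time to successful eradication, long-term antimicrobial resistance". The Follow-up section sets a one-year follow-up, foresees stopping of study treatment, and makes the final visit conditional on feasibility. It also says that at inclusion and at 6 and 12 months "generic health-related quality of life and health care costs will be measured with questionnaires as well".

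**The concern.** The sentence reads as a closed list. Choosing by type of outcome and distribution only selects among four tests, and none of them takes a censoring indicator or an exposure time. An analysis plan that follows the sentence inherits the problem; one that departs from it contradicts the published protocol.

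The outcomes at issue carry the clinical message. The Discussion says the trial will determine what each strategy contributes to reducing catheter-related bloodstream infections. The Cost-effectiveness analysis section expects few infections, so most patients will be censored for time to infection, by the end of the year, by withdrawal or by death. The Background reports infections per 1000 catheter days, yet the comparison section uses no exposure denominator.

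The arms are open-label and very different: short two-drug systemic cycles against monthly topical courses. Unequal withdrawal is therefore plausible. It could then appear as a difference in infection.

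**Working it through.** **Plan's own figure.** The article gives no figure for the secondary analyses. Its sample size supplies the arm size used here and reproduces with the unpooled formula: (1.96 + 0.8416)² × (0.55×0.45 + 0.77×0.23) / 0.22² = 7.849 × 0.4246 / 0.0484 = 68.86, so 69 per arm and 138 in total. The sample size is not in question.

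**Inputs from the article.** 69 per arm; one year of follow-up; two-sided 5%; 0.38 to 4.58 infections per 1000 catheter days (Background). Per year this is 0.38 × 365/1000 = 0.139 to 4.58 × 365/1000 = 1.67.

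**Assumed inputs.** Withdrawal percentages, the 80% exposure ratio, the middle rate of 1.5 per 1000, and the baseline correlation. None is in the article.

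**Step 1: time to first infection, no true difference.** Event and withdrawal times are exponential and independent, cut off at one year. Withdrawal hazard = −ln(1 − one-year withdrawal proportion). Percentage of trials rejected by Wilcoxon on observed follow-up time (1,500 trials per cell):

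| Infection hazard per year | 10% v 20% withdrawal | 5% v 30% withdrawal |
|---|---|---|
| 0.139 | 21 | 81 |
| 0.2 | 17 | 73 |
| 0.5 | 11 | 43 |
| 1.67 | 6 | 12 |

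Log-rank rejects in about 4-6% throughout. With equal withdrawal (none, or 10% in both arms), Wilcoxon rejects in about 5% and so does log-rank. Simulation error in the 21% cell is √(0.21 × 0.79 / 1500) ≈ 1 point, and repeat runs of that cell gave 19-24%; 11-22% is a fair summary for hazards of 0.139-0.5.

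The inflation is largest at low hazards because few times then end in infection. At 0.139 per year the one-year risk is 1 − exp(−0.139) = 13%, so withdrawals make up much of the short times being ranked.

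**Step 2: counts, no true difference in rate.** Poisson counts, with one arm having 80% of the other's catheter-days (2,000 trials per row):

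| Rate per 1000 catheter-days | t-test | Wilcoxon | Exact rate test using exposure |
|---|---|---|---|
| 0.38 | 6.7% | 6.8% | 3.5% |
| 1.5 (assumed) | 15.6% | 13.9% | 4.4% |
| 4.58 | 35.9% | 33.9% | 5.2% |

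With equal exposure, t and Wilcoxon reject in about 5% and the rate test in about 4%.

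**Step 3: EQ-5D-5L.** Adjusting for baseline multiplies the variance by 1 − r². At r = 0.5 this is 0.75 and at r = 0.7 it is 0.51, a cut of 25-49%. It does not change type I error.

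**Step 4: time to successful eradication.** Under Study intervention, search and destroy is swabbed weekly for 3 weeks after a one-week cycle, so success can be declared at about 1 + 3 = 4 weeks. Continuous suppression has its first standard swabs at month 3. The gap is about two months by schedule alone. Success as three consecutive negative sets is defined for the search and destroy arm only.

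**The case against.** The strongest reply is that the sentence is generic, names none of these outcomes, and stands in a condensed article whose analysis plan is not shown. Matching a model to each secondary outcome is normal analysis-plan content. That would answer a complaint of silence. Here the article does say how the comparisons will be made, and no test on its list fits.

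Three replies limit the size.

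- The inflation needs unequal withdrawal or exposure, and the article reports neither. Infections and catheter removals are also taken from electronic patient files, so stopping treatment need not end observation.
- It depends on ranking observed follow-up times, which in effect counts a withdrawal as an infection on that day. The article does not state this coding. Setting event-free patients to one year gives about 5-7% (8% in a re-run at hazard 0.5 with 5% v 30% withdrawal). Using infected patients only gives about 5-6% at 10% v 20%, but discards every event-free patient.
- Chi-square on any infection is barely inflated at the low event rate (about 5.4%).

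All three stand. They make the size conditional; they do not make the listed tests suitable.

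A reader might also infer that infections will be reduced to a percentage of patients. The article does not support this: it applies that summary to dichotomous outcomes and lists catheter-related bloodstream infections among continuous data.

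**Conclusion.** The point holds as a badly fixed method for secondary outcomes. The named tests cannot handle censoring in time to first catheter-related infection, or unequal exposure in infection incidence and catheter removals. The consequence is conditional. Type I error is about 5% when follow-up is equal. For Wilcoxon on observed times at hazards of 0.139-0.5 per year it is about 11-22% at 10% versus 20% withdrawal and 43-81% at 5% versus 30%. A 20% shortfall in catheter-days gives about 7-36% for t or Wilcoxon on counts across the article's own infection range. The splits are assumptions, and withdrawal was taken as unrelated to infection risk; log-rank would not be protected if it were related.

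Two stronger readings do not hold. Leaving out baseline EQ-5D-5L does not create false differences in a randomised comparison; it loses precision. Nor is time to successful eradication a matter of test choice: its problem is the swab schedule, and log-rank would not cure it. The primary analysis is untouched, so this should be corrected but does not undermine the trial's main conclusion.

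**What to change.** Replace the single sentence on between-group tests with methods by type of outcome:

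- Time to first catheter-related infection: Kaplan-Meier with log-rank, or Cox regression, stratified by country as in the randomisation. Treat death as a competing event and state the rules for censoring at withdrawal and at one year.
- Infections and catheter removals: Poisson or negative binomial regression with log catheter-days (or follow-up time) as offset. The negative binomial allows for patients with repeated events.
- EQ-5D-5L at 6 and 12 months: adjust for the inclusion value, as a gain in precision.
- Time to successful eradication: compare only on the common 3, 6, 9 and 12-month swabs with one definition for both arms, or drop it. Bring the Abstract and Table 1 into line.
- Simple binary outcomes: keep chi-square or Fisher.

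The cost is protocol wording and slightly more programming. Catheter-days are not among the listed data items, so they would have to be derived from patient records; follow-up time is the fallback. Baseline EQ-5D-5L is already collected.
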